*The Food Friends* program is one such intervention that has addressed developmental behaviors in young children. Comprised of two components *– Fun with New Foods®* and *Get Movin’ with Mighty Moves®* - the program has successfully demonstrated increases in both children’s willingness to try new foods (food preference) and gross motor performance in preschool-aged children [15,16]. Further exploration is warranted to understand social and environmental influences on these behaviors.

Children’s eating and activity behaviors are influenced by factors that are individual to the child, but also by the environments, in which they live, learn and play. Ecological models provide a framework for addressing interactions across individual, social and environmental spheres of influence [17,18]. Predictive behaviors within these environments can influence child behaviors. While many predictive behaviors have been shown to influence dietary intake, physical activity, and weight status; food preference and motor performance merit further exploration. Understanding the context in which child behavioral patterns are developed is critical to developing a model to address childhood obesity. Skouteris [19] makes the argument that children’s development is a bidirectional transaction, with parents influencing children but also children impacting parents’ decisions and behaviors. Understanding environments, parent behaviors and children’s behaviors over time will provide an opportunity to begin to develop transactional models.

The Colorado Longitudinal Eating And Physical activity (LEAP) Study utilizes a social ecological approach to explore individual, family and environmental factors and their relationship to child weight status over a 3 year timeframe. Our primary research questions are as follows:

1. Are behavior changes (e.g. increased willingness to try new foods and improved gross motor skills) positively influenced by a preschool nutrition and activity program, *The Food Friends®*, sustained through early elementary school?

2. Do *The Food Friends®* programs have an impact on reducing the percentage of children considered overweight and/or obese over a 3 year timeframe?

3. Do food preference and gross motor performance directly affect child weight status or are they mediators to dietary intake and physical activity?

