**Figure 2 F2:**
[figure not shown]
**Conceptual model for the Colorado LEAP study.** This model illustrates a multidimensional approach to addressing healthy growth in young children. The bottom of the figure depicts the intervention’s impact on Eating and Physical activity-related behaviors which then may influence Diet, Physical Activity, and Growth. These behaviors occur in multiple environments (micro-, meso-, & macrosystems; colored boxes) that are influenced by roles and social norms. Individual and environmental characteristics (black font) may interact with behaviors, practices, and/or policies (white font) to influence healthy growth. The items listed in the white font in the Child characteristics and Home environment boxes are the outcome measures used in this study.

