To assess whether preference and motor performance directly affect child weight status or serve as mediators to dietary intake and physical activity as they affect child weight (Question 3), three prediction models will be tested beginning with the use of a hierarchical multiple regression analysis. In both prediction models, measures representing concepts of Davison and Birch’s ecological model of child weight status serve as predictors (i.e. independent variables) with measures of child characteristics and child risk factors entered first (step 1), and measures of parenting styles and family characteristics in the next step, (step 2). The prediction models will differ in their inclusion or exclusion in step 1of (a) dietary intake and physical activity measures or (b) taste preference and motor performance or (c) the combination of dietary intake, physical activity measures, taste preference and motor performance. Changes in the beta weights of these variables across the 3 predictor models will be examined to determine the relationships of taste preference to dietary intake and motor performance to physical activity measures.

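### Question 3: comparing beta weights across three regressions of child weight does not separately estimate the preference-to-diet and motor-to-activity relationships, and it cannot establish causal order

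*Protocol article*

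**What the plan says.** Question 3, listed in the Background among the primary research questions, asks: "Do food preference and gross motor performance directly affect child weight status or are they mediators to dietary intake and physical activity".

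The Data analysis section repeats the alternative, asking whether preference and motor performance act directly or "serve as mediators to dietary intake and physical activity as they affect child weight". It then says that "three prediction models will be tested beginning with the use of a hierarchical multiple regression analysis". Child weight is the outcome throughout. Child characteristics and risk factors enter at step 1, and parenting and family measures at step 2. The models differ in what else step 1 contains. The first two options are given as "a) dietary intake and physical activity measures or (b) taste preference and motor performance"; the third option is "c) the combination of dietary intake, physical activity measures, taste preference and motor performance".

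The rule for drawing the conclusion is the last sentence: "Changes in the beta weights of these variables across the 3 predictor models will be examined to determine the relationships of taste preference". That sentence pairs preference with diet, and motor performance with activity. The section names no indirect effect and assigns no wave to predictor, mediator or outcome. The Study design section gives four assessments: fall and spring of preschool, spring of kindergarten, and spring of 1st grade.

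The Figure 2 caption says the intervention acts on eating and activity-related behaviors, "which then may influence Diet, Physical Activity, and Growth".

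**The concern.** The stated rule is meant to determine how preference relates to diet and how motor skill relates to activity. Yet in all three models these four variables appear only on the predictor side. A relationship between two predictors can show up only indirectly, through how their coefficients on weight shift when they are entered together. With two candidate mediators, several sets of paths can produce the same shift.

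The direction also matters. If preference lies upstream of diet, the informative change is in the preference beta from model (b) to model (c). If preference carries the effect of diet, it is the change in the diet beta from (a) to (c). The text does not say which is meant. A primary question could therefore be reported as mediation through diet when no preference-to-diet path exists, or the reverse.

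**Working it through.** The article gives no figure for Question 3, so there is none to reproduce. The check is algebraic. The three model structures come from the Data analysis section; every path value below is an assumption chosen for illustration.

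**Notation.** P is preference, M motor performance, D diet, A activity and Y child weight, all standardised. P and M are uncorrelated, and the other covariates are left out. Write PD for the P-to-D path, and likewise PA, MD and MA. Direct effects on Y: P −0.1, M +0.1, D +0.3, A −0.3.

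**Formulas.** Model (c) returns the four direct effects. In model (b):

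- beta of P = direct P + PD × 0.3 + PA × (−0.3)
- beta of M = direct M + MD × 0.3 + MA × (−0.3)

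In both structures below D and A are uncorrelated, so in model (a) each beta is the direct effect plus (correlation with P) × direct P plus (correlation with M) × direct M.

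**Structure 1, own paths only:** PD = 0.4, MA = 0.4, PA = MD = 0.

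**Structure 2, cross paths only:** PD = 0, MA = 0, PA = −0.4, MD = −0.4.

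| Model | Beta | Structure 1 | Structure 2 |
|---|---|---|---|
| (a) | D | 0.3 + 0.4 × (−0.1) = 0.26 | 0.3 + (−0.4) × 0.1 = 0.26 |
| (a) | A | −0.3 + 0.4 × 0.1 = −0.26 | −0.3 + (−0.4) × (−0.1) = −0.26 |
| (b) | P | −0.1 + 0.4 × 0.3 = 0.02 | −0.1 + (−0.4) × (−0.3) = 0.02 |
| (b) | M | 0.1 + 0.4 × (−0.3) = −0.02 | 0.1 + (−0.4) × 0.3 = −0.02 |
| (c) | P, M, D, A | −0.10, 0.10, 0.30, −0.30 | −0.10, 0.10, 0.30, −0.30 |

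The preference-to-diet path is 0.4 in one structure and 0 in the other, and every beta agrees. From (b) to (c) the preference beta changes by 0.02 − (−0.10) = 0.12. That is 0.4 × 0.3 through diet in structure 1, and (−0.4) × (−0.3) through activity in structure 2. Regressing D on P and M would return 0.4 or 0 for P and separate the two at once.

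**How special is this?** Agreement in (b) and (c) does not depend on the direct effects of P and M. Agreement in (a) does. With direct M at −0.1, structure 1 gives (a) 0.26, −0.34 and structure 2 gives 0.34, −0.26. The example shows that the paths need not be recoverable, not that they never are.

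**Causal order.** Keep all direct effects as above except M = −0.1, and set the P–D and M–A associations to 0.4. Three explanations of those associations were compared: P causes D and M causes A; D causes P and A causes M; an unmeasured common cause of each pair. All three give

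- (a) D 0.26, A −0.34
- (b) P 0.02, M −0.22
- (c) P −0.10, M −0.10, D 0.30, A −0.30

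A simulation of 400,000 records per structure agreed to within about 0.003.

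**The case against.** The strongest reply is that the comparison is not empty. In linear regression on the same records and covariates, the (b)-to-(c) change in the preference beta is the total indirect effect, and the model (c) beta is the direct effect, provided the causal order is assumed and there is no unmeasured confounding. With a single pair, the betas even recover the path: for correlations of 0.5 (preference, diet) and 0.4 (diet, weight) with no direct effect, (0.20 − 0.00) / 0.40 = 0.50. All of this stands. A reader might infer that the analysis cannot answer Question 3 at all; that goes too far.

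Three other strong readings are also unsupported:

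- *That failing to separate mediation from confounding is peculiar to this plan.* Any analysis of same-wave observational data has that limit, a path model included. Time order helps, but it does not remove unmeasured common causes.
- *That the predictors are unlagged, or the regression is the only analysis.* The section is silent on waves, and the Discussion speaks of prediction across time. The regression is introduced as a beginning. However, no later step is named, and the last sentence makes the beta comparison itself the means of determining the relationships.
- *That Question 3 contradicts Figure 2.* Only the caption is available. It places eating and activity-related behaviors before diet and activity. Calling preference and motor skill mediators to diet and activity can be read as placing them between intervention and diet, which agrees. The wording is ambiguous, not shown to be wrong.

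An article may leave detail to an analysis plan, but here it fixes both the models and the inferential rule.

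**Conclusion.** The concern holds in a limited form. The stated comparison does not separately estimate the two relationships it is meant to determine, and it cannot establish their causal order. In the illustration, a preference-to-diet path of 0.4 and one of 0 are indistinguishable across all three models. This rests on assumed path values, linear models and the omission of other covariates; the trial's actual correlations are not in the document.

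The beta change can be read as a total indirect effect only under an assumed order and no unmeasured confounding, and the section states neither. The direction of mediation needs clarifying. So does the number of models: the paragraph announces three, then uses a word that implies two, then returns to three.

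The analysis should be amended because the question is primary and the data needed are already planned.

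**What to change.** 1. State the intended direction of mediation in Question 3 and in the Data analysis section, consistently with Figure 2. The choice belongs to the authors. Correct the count of models.
2. If preference and motor skill are meant to be upstream, add regressions of diet on earlier preference and of activity on earlier motor skill. Include both upstream variables in each, so that own and cross paths are separated. Then regress 1st-grade BMIz on all four.
3. Measure preference and motor skill at an earlier wave than diet and activity, for example end of preschool and then kindergarten. Adjust for baseline BMIz and baseline values of the mediators.
4. Report direct and specific indirect effects with confidence intervals, labelled exploratory and conditional on no unmeasured confounding. Give the reverse ordering as a sensitivity analysis.
5. Account for site by adjustment. Five communities (2 intervention, 3 control) are too few for a dependable cluster bootstrap, and the report should say so.
6. Keep the three hierarchical regressions as description.

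The cost is more analysis work, with no new data collection. Intervals for the indirect effects will be wide, and time ordering will still not exclude unmeasured common causes.

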#### Food frequency

The Block Kids Food Screener (Ages 2 – 17) will be used to measure parent reports of their child’s food intake. This food screener assesses children’s intake by food group and reports outcomes in number of servings and calories consumed [41,42].

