### Physical activity

#### Physical activity levels and intensity

Pedometers and accelerometers will used to assess physical activity (PA). Two Walk-4-Life pedometer (Model W4L Classic; Plainfield, IL), with safety strap, will be sent home along with a log to record the number of daily steps. Parents will be asked to place the pedometer on the child and themselves when the child/parent gets out of bed and to take it off when the child/parent goes to bed. They will be asked to record the number of total steps taken each day for six days – four weekday and two weekend days. Parents will also be asked to record notes about if the child/parent did not wear the pedometer for a specific time during the day, what types of activities they participated in, etc. A subsample of participants will be asked to wear an Actical accelerometer (Phillips – Respironics, Oregon, USA) to measure time spent in various intensities of PA as well as time spent in activity at school versus home. The accelerometer will be attached on the non-dominant wrist of each student with semi-non-removable band to measure PA. The Actical is a small, lightweight, waterproof, omni-directional accelerometer. It will be placed on the child during the school day. Children will be asked to wear the accelerometer for a 6-day period and to maintain “typical” activity patterns. To encourage compliance in wearing the accelerometers, the children and parents will be given written and verbal instructions.

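### Question 3 compares preference and motor betas with and without diet and activity in the model, but error in the diet and activity measures can leave part of a fully mediated effect looking direct

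*Protocol article*

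**What the plan says.** The Background lists the direct-or-mediated question as the third of three primary research questions. Data analysis restates it as whether preference and motor performance affect child weight directly "or serve as mediators to dietary intake and physical activity as they affect child weight". The method follows: "three prediction models will be tested beginning with the use of a hierarchical multiple regression analysis". The models differ in what enters at step 1:

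- (a) diet and activity;
- (b) taste preference and motor performance;
- (c) "the combination of dietary intake, physical activity measures, taste preference and motor performance".

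Then "Changes in the beta weights of these variables across the 3 predictor models will be examined", with the stated aim of learning how preference relates to diet and how motor performance relates to activity.

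The legend of Figure 2 gives the causal order, with the intervention acting on "Eating and Physical activity-related behaviors which then may influence Diet, Physical Activity, and Growth". Diet and activity are therefore the intermediate variables.

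For diet, the Food frequency section names a screener that "will be used to measure parent reports of their child’s food intake". For activity, parents are asked to "record the number of total steps taken each day for six days" (Physical activity levels and intensity). The article also plans weighed intake of two target foods (Consumption of program target foods) and accelerometry in a subsample. The text on Question 3 does not say which of these enter the models. It gives no reliability for the screener or the step log, and it describes no allowance for error in either.

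**The concern.** Comparing a predictor's beta with and without a mediator separates direct from indirect effects only when the mediator is measured without error (and mediator and outcome are not confounded). If the measured mediator is noisy, adjusting for it removes only part of the indirect effect. The remainder stays on the predictor and looks like a direct effect.

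Sample size does not cure this: more children give a more precise estimate of the same biased quantity. The stake is the reading of a primary research question. A beta for preference or motor skill that persists in model (c) could be a real direct effect or the product of noise in the diet and activity measures, and the planned comparison cannot tell these apart.

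**Working it through.** The plan states no figure on this point, so there is none to reproduce. The check asks how much of a fully mediated effect would remain on the predictor in model (c).

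**Inputs**

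- Causal order preference or motor skill → diet or activity → weight: from the Figure 2 legend.
- Conditioning on the measured mediator: model (c) in Data analysis.
- Reliability L of the mediator measure: not in the documents; assumed 0.5 to 0.8, with other values shown.
- Correlation a between predictor and true mediator: not in the documents; assumed 0.3 to 0.5.
- Form of error: assumed classical and non-differential, with one mediator per path and no confounding of mediator and weight.

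**Formula.** Let X (predictor) and M (true mediator) have unit variance and correlation a. Let Y = bM + error, with no direct path. The measured mediator is W = M + u, so var(W) = 1/L. Then cov(X,W) = a, cov(X,Y) = ab and cov(W,Y) = b. The coefficient of X given W is

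(ab/L − ab)/(1/L − a²) = ab(1−L)/(1−L·a²).

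The total effect is ab, so the share left as apparently direct is (1−L)/(1−L·a²). It is never below 1−L and is zero only when L = 1.

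**Numbers**

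| L | a = 0.3 | a = 0.5 |
|---|---|---|
| 0.5 | 0.5/0.955 = 52.4% | 0.5/0.875 = 57.1% |
| 0.7 | 0.3/0.937 = 32.0% | 0.3/0.825 = 36.4% |
| 0.8 | 0.2/0.928 = 21.6% | 0.2/0.800 = 25.0% |
| 0.9 | 0.1/0.919 = 10.9% | 0.1/0.775 = 12.9% |

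Over the same range of a, L = 0.95 gives 5.5% to 6.6% and L = 0.3 gives 71.9% to 75.7%. The result depends mainly on L; a matters little.

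**Simulation check** (1,000,000 records per setting). The share was 21.5% at L = 0.8, a = 0.3 and 57.2% at L = 0.5, a = 0.5, in agreement with the formula. With the error-free mediator it was about zero.

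**Differential error.** At L = 0.65 and a = 0.4 the classical share is 0.35/0.896 = 39%. Letting the reported mediator shift by −0.3 to +0.3 SD per SD of the predictor moved the share from about 85% to −7%. The same shift per SD of the outcome moved it from about 92% to −6%.

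**Visibility at the planned size.** With 180 children (90 per group after attrition, from Sample size estimation) and assumed mediator effects of 0.2 to 0.4 SD, a two-sided 5% test of the false direct effect rejected in about 5% of simulated trials at L = 0.8, a = 0.3. At L = 0.5, a = 0.5 it rejected in 12% to 31%.

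**The case against.** Several stronger readings are tempting, and the documents do not support them.

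- *That the plan decides 'direct' from whatever remains in model (c).* It sets no such threshold. It says changes will be examined, and that testing begins with this regression. On a criterion of change, a fully mediated beta would still fall by about 43% to 78% between models (b) and (c) under the main assumptions (100% minus 57% and 22%), which points towards mediation. This stands: the weakness is that the comparison is ambiguous, not that a wrong rule is written down.
- *That diet and activity are simply what parents record.* This fits the screener and the step log only. The weighed foods and the accelerometer data are not parent-recorded. However, one covers two foods and the other a subsample, and neither is error-free. If several measures enter together, the single-mediator formula is only a guide.
- *That 22% to 57% is a property of this trial.* It follows from assumed values. The article quotes reliabilities for other instruments, such as a test-retest value of 0.74 for a parent-rated food scale, but none for the two measures at issue.
- *That Question 3 is bound to tilt towards 'direct' and be answered wrongly.* Differential reporting could shrink or reverse the bias, and a significant false direct effect is the minority result at the planned size even in the worst corner checked. Yet the Question 3 text names no test for the change in betas. The sizes of the betas are what will be examined, and under classical error those sizes are biased at any sample size.

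It can also be said that measurement-error handling belongs in a fuller analysis plan. As a demand for missing detail, the point would fail. It survives because the comparison that the article does state has this limitation built in.

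**Conclusion.** The point holds in a limited form. The stated comparison for a primary research question can show an apparent direct effect of preference or motor skill when the whole effect runs through diet or activity, and it offers no means of telling the two apart. Under classical, non-differential error, one mediator per path and no mediator–weight confounding, the apparent direct share is about 22% to 57% for assumed reliabilities of 0.5 to 0.8 and correlations of 0.3 to 0.5. It is about 11% to 13% at reliability 0.9. Relaxing the assumption about the type of error leaves both size and sign open. This is a reason to read model (c) cautiously and to show its sensitivity. It does not show that the planned answer will be wrong.

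**What to change.** In the Question 3 part of Data analysis:

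1. Add a sensitivity analysis that reports the model (c) betas for preference and motor performance corrected for diet and activity reliabilities over a stated range, for example 0.5 to 0.9, with 1.0 as the uncorrected case.
2. State that a residual beta in model (c) will not by itself be read as a direct effect.

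No new data are needed. The cost is a little more analysis work, wider intervals for the corrected betas and a more cautious conclusion. The point does not require calibrating the step log against the accelerometer, using a latent variable or a mean over waves, or making an effect persist across the whole range before it is called direct. Each of these is open to dispute, and the sensitivity analysis works without them.

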## Discussion

Currently, studies are beginning to examine behaviors and correlates related to children’s weight status across multiple levels of the social ecological model [58], however most have been cross-sectional in nature [7,59]. Longitudinal studies are needed to identify causal influences of children’s dietary and physical activity behaviors as well as on growth [19]. Examining eating and activity behaviors longitudinally, and in multiple environments, can provide insights into relationships between predictive behaviors and dietary, physical activity and weight outcomes.

The Colorado LEAP study utilized Davison and Birch’s ecological model of childhood obesity as a springboard for the design of the study, which allows for longitudinal exploration of relationships among eating habits, physical activity patterns, and weight status within and across spheres of the social ecological model. The methods represent an advance in study design as they will allow not only for interaction among spheres but will do so predictively across time. In addition to the primary study outcomes examining behavior changes in children, the design allows for exploration into what parents report at baseline and its impact on child behaviors over time, and conversely child behaviors at baseline and the impact on parent response at future time points. Examining the data in this way supports Skouteris et al.’s [19] viewpoint of children’s development being bidirectional.

Key strengths of this study include utilization of a multi-disciplinary approach and a longitudinal design embedded within a social ecological framework. A further strength is that the recruitment strategy includes both boys and girls from ethnic minority populations in rural areas and will provide insights into obesity prevention effects on these at risk populations. It should be noted that while schools based in rural communities were purposefully chosen as study sites, a limitation is that we do not include a measure assessing the obeseogenic environment at the community level. Ultimately, the design of the Colorado LEAP Study has the potential to inform strategies for childhood obesity interventions in early childhood.

